There have also been a few clinical trials that explored the effectiveness and safety of JUG in RD. Patients undergoing RT for brain tumors showed favorable improvement or meaningful prevention of scalp dermatitis after topical application of JUG.^[18,19]^ A pilot study randomly allocated 30 breast cancer patients and evaluated the incidence of RD with Radiation Therapy Oncology Group (RTOG) toxicity of grade 2 or more, resulting in lowering of the RD incidence in the JUG treatment group with no safety issues, as compared to the general supportive care (GSC) group.^[20]^

This study protocol is primarily aimed at showing the effectiveness and safety of the adjuvant application of JUG for RD in breast cancer patients undergoing RT, as compared to GSC, along with its pharmacoeconomic evaluation.

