### Study design and setting

2.2

This is a prospective, open-label, parallel-group, randomized controlled trial. This study will enroll 80 female patients, who have been diagnosed with unilateral breast cancer confirmed by biopsy and supposed to undergo RT of 50 to 64 Gy dose after breast conserving surgery. They will be allocated to either the JUG or GSC group with an allocation ratio of 1:1. Both groups will be subjected to GSC, but only the JUG group will apply the adjuvant JUG ointment on the irradiated skin for 6 weeks, twice a day. Eligible participants will be enrolled from the in-patients or out-patients of the Kyung Hee University Korean Medicine Hospital, Seoul, Republic of Korea. Study advertisements will be posted on webpages and notice boards to promote subject enrollments.

The study flow is depicted in Figure 1.

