### Randomization, allocation concealment, and blinding

2.4

An independent statistician will generate random sequence numbers using the R version 3.5.2 (The R Foundation) with blockrand package version 1.3. Eligible participants will be randomly allocated to either the JUG or GSC group in a ratio of 1:1, and the allocation will be concealed using the sealed envelope method. The sealed envelopes will include random numbers and allocated groups, and the investigators will open the envelopes to assign the participants to particular groups after completing the screening process. Since JUG will be prescribed only to participants of the JUG treatment group, this trial is an open-label study.

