### Radiation therapy and general supportive care

2.6

All the patients will undergo RT at a dose of 2 Gy/day without bolus by a medical specialist of radiation oncology. The whole breast irradiation with photon beam will be implemented for 5 weeks (5 times a week) and a boost irradiation with photon or electron beam will be added for 1 week (5–7 times a week), if necessary. Additionally, the regional lymph node irradiation could be included, covering axilla level II/III for irradiation.

Participants allocated to the treatment or control group will be instructed to wash the irradiated skin with clean water or wet towels, and wipe the skin with dry towels in order to keep the irradiated skin clean and dry. Furthermore, any lotion or cream can be applied to the breast skin. This GSC regimen is based on a preceding study^[9]^ and a pilot trial.^[20]^

Any other type of preventive or treatment management of RD is prohibited during study participation.

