### Safety assessment

2.11

The adverse events will be evaluated and reported during the study. Local rash, rubescent, or itching are expected to be found from time to time. If an adverse reaction is found, then the investigators will assess the intensity/frequency of each episode and decide whether further treatments are necessary or not. Vital signs will be regularly checked to assess JUG safety.

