### Statistical analysis

2.14

The primary outcome is the incidence rate of RD graded 2 or more on the RTOG toxicity scale. These results will be statistically compared between groups using the logrank test after estimating the survival curve with Kaplan–Meier method. Any continuous variables will be tested independently with *t* test or Mann–Whitney *U* test according to the normality of the distribution. The adverse events will be tested with Chi-square or Fisher exact test. Paired *t*test or McNemar test will be adopted to compare the vital signs results within a group. All the data will be analyzed at a significance level of .05 (two-sided) with R software version 3.5.2 or later.

The primary analysis will include all the participants assessed with the RTOG toxicity scale at least once after randomization (full analysis set). Secondarily, per protocol set will be analyzed, which is defined as the group of participants complying with the trial procedure, including the study drug use, at least 80%. Safety set is defined as the participants who use the study drug at least once.

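### The only test named for vital signs compares them within an arm, which cannot separate Jaungo from radiotherapy or time; a between-arm comparison should be stated.

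*Protocol article*

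**What the plan says.** Section 2.11 (Safety assessment) gives the purpose: "Vital signs will be regularly checked to assess JUG safety". Section 2.14 (Statistical analysis) gives the method. It names the paired t test and its categorical counterpart: "McNemar test will be adopted to compare the vital signs results within a group". No other sentence names a test for vital signs.

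Three other statements in the article bear on this:

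- **The aim is comparative.** The Introduction describes the study as "primarily aimed at showing the effectiveness and safety of the adjuvant application of JUG for RD in breast cancer patients undergoing RT, as compared to" general supportive care (GSC).
- **The design supplies the comparison.** Section 2.4: "Eligible participants will be randomly allocated to either the JUG or GSC group in a ratio of 1:1". Section 2.2: "Both groups will be subjected to GSC, but only the JUG group will apply the adjuvant JUG ointment".
- **Radiotherapy is common to both arms.** Section 2.6: "All the patients will undergo RT at a dose of 2 Gy/day without bolus". It runs for 5 weeks, with a boost week if needed, and section 2.5 has JUG applied for 42 days over that same period.

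Section 2.14 also contains a general rule, "Any continuous variables will be tested independently with" the t test or Mann–Whitney U test. It assigns the Chi-square or Fisher exact test to adverse events and defines the safety population: "Safety set is defined as the participants who use the study drug at least once".

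**The concern.** A paired test within the JUG arm asks whether vital signs moved between two time points in patients who were having radiotherapy and using JUG. It does not ask whether JUG moved them. Radiotherapy, time and regression to the mean all enter the same change score.

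Running the paired test in each arm and setting the two p-values side by side does not repair this. A result that crosses 0.05 in one arm and misses it in the other is common when the two arms behave identically.

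An error in either direction is possible. A drift that both arms share could be reported as a JUG safety signal. A JUG effect that runs against the shared drift could be hidden by it. The randomised GSC arm, which would remove the shared part, is not used in the test that the vital-sign sentence prescribes.

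**Working it through.** **1. Number per arm.** The plan states 36 per group and 40 after allowance for dropout (section 2.13). This figure concerns the primary outcome and is not in dispute. It is needed here only as the n, and it reproduces:

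- Hazard ratio = ln(0.533) / ln(0.214) = 0.408.
- Freedman events at two-sided 0.05 and 80% power = (1.960 + 0.842)² × [(1 + 0.408) / (1 − 0.408)]² = 44.4, rounded up to 45.
- Mean event probability = 1 − (0.533 + 0.214)/2 = 0.6265, so 45 / 0.6265 = 71.8 patients, or 36 per group.
- 36 / 0.9 = 40 per group.

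**2. What each test estimates.** Let m be the mean change that both arms share (radiotherapy, time, regression to the mean) and j the added effect of JUG.

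- Paired test in the JUG arm: estimates m + j.
- Paired test in the GSC arm: estimates m.
- Between-arm comparison of change: estimates (m + j) − m = j.

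Only the third isolates j. The same reasoning applies to McNemar's test for a categorised vital sign, since a shift in the proportion abnormal within an arm also contains the shared part.

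**3. How often the paired test is significant when j = 0.** Inputs: n = 36 per arm, two-sided 0.05 (section 2.14), and a shared shift of d SDs of the change score. The documents give no vital-sign means or SDs, so d is an assumption and is shown as a range. Change scores are taken as normal with equal variance.

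P(significant in JUG arm) = P(|T| > t₀.₉₇₅,₃₅), where T is noncentral t with 35 degrees of freedom and noncentrality d√36 = 6d. Call this p. The arms are independent, so P(exactly one arm significant) = 2p(1 − p).

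| Shared shift d | Noncentrality 6d | p, paired test in JUG arm | 2p(1 − p), exactly one arm significant | Between-arm t test on change |
|---|---|---|---|---|
| 0 | 0 | 5.0% | 9.5% | 5% |
| 0.2 | 1.2 | 21.5% | 33.7% | 5% |
| 0.3 | 1.8 | 41.7% | 48.6% | 5% |
| 0.5 | 3.0 | 83.1% | 28.1% | 5% |

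The between-arm column is 5% because the shared shift cancels. A simulation of 100,000 trials gave 5.0%, 4.9% and 4.9% at d = 0, 0.3 and 0.5. With all 40 per arm analysed, the paired-test figures are 23.5%, 45.7% and 86.9% at d = 0.2, 0.3 and 0.5.

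By symmetry, half of the fourth column is the pattern most likely to be misread, JUG significant and GSC not: 33.7/2 = 16.9% at d = 0.2 and 48.6/2 = 24.3% at d = 0.3.

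**The case against.** The strongest reply is that a between-group test may already be intended. The general rule in section 2.14 covers continuous variables without exception, and the abstract calls its test the independent t test. Blood pressure or pulse would be continuous, so the vital-sign sentence could be an added within-arm check. This stands as a possible reading, and it rules out the inference that the plan excludes any between-arm test of vital signs. It does not settle the matter. The specific sentence follows the general one and prescribes a within-group comparison without saying that it is additional. The general rule also offers nothing for categorised vital signs, for which McNemar's test is the only one named.

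A reader might also infer that the safety objective as a whole ignores the randomised comparison. The documents do not support that: adverse events have their own Chi-square or Fisher exact test. The safety set, read literally, holds only users of the study drug and so no GSC participants. That makes a between-arm vital-sign comparison less certain, but it does not show that none is planned.

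The article condenses a fuller protocol, and a statistical analysis plan may exist. The lack of a detailed model is therefore no fault. The point rests on a method that the article does name, and that method does not answer the stated question.

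The time points are not given. Section 2.11 says only that the checks are regular, and the study-flow figure is not shown. That the paired tests compare values before and after treatment is inferred from the choice of test.

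Finally, vital signs are a supporting safety measure for a topical ointment. That is a fair argument about priority.

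**Conclusion.** The point holds in limited form. The analysis named specifically for vital signs cannot attribute a change to JUG, although the trial has a randomised control arm and a comparative safety aim. If JUG has no effect and both arms shift by 0.2 to 0.5 SD of the change score, the paired test in the JUG arm is significant in about 22% to 83% of trials at 36 per arm, against about 5% for a between-arm test. With no shared shift, both are at 5% and the paired test does no such harm. The size therefore depends wholly on an assumed drift that the documents do not inform.

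Whether a between-group test of continuous vital signs is also intended is unclear, and the article should say. Severity is minor. The primary analysis, the sample size and the adverse-event test are unaffected.

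**What to change.** In section 2.14, replace the vital-sign sentence with one that states a comparison between the JUG and GSC arms:

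- **Continuous vital signs:** compare change, or the follow-up value, adjusted for the pre-treatment value (for example by ANCOVA), and report the difference with its 95% confidence interval. A two-sample comparison of change would also remove the flaw.
- **Categorised vital signs:** compare proportions between arms with Fisher's exact test.
- **Population:** say that GSC participants are included in this safety comparison, since the present safety-set wording can be read to leave them out.
- **Within-arm changes:** report as description, without p-values.

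Name the pre-treatment and follow-up time points to be used. The cost is a few lines of text before analysis. If vital signs are recorded in both arms on the same schedule, no new data are needed, and nothing in trial conduct changes.

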### Eligibility criteria

2.3

Female patients aged 19 to 80 years old and diagnosed with unilateral breast cancer based on biopsy are eligible for participation in this study. The other inclusion criteria include: RT with a total dose of 50 to 64 Gy without bolus, after breast conserving surgery; and Eastern Cooperative Oncology Group performance status of 1 grade or less. All the eligible participants have to provide voluntarily signed written/informed consent forms after understanding the trial details.

The exclusion criteria are: inflammatory breast cancer; skin invasion or distant metastasis of tumor; concurrent chemotherapy with RT, except for herceptin and hormone therapy; untreated wounds, severe/extensive burn, dampness, erosion, or suppuration on breast skin; fever; history of prior RT to the chest wall; history of connective tissue disorders; history of heart diseases such as arrhythmia, uncontrolled hypertension, severe mental disorders (dementia, drug addiction, etc.) demanding intensive treatment, or paralysis; or history of hypersensitivity reaction to the study drug or it is ingredients. Participants who are involved in other trials within that month or disagree with contraception during the study period will also be considered ineligible.

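### The safety set is defined by use of the study drug, so as written it holds no GSC patients and leaves the adverse-event comparison without a control group

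*Protocol article*

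**What the plan says.** Section 2.14 (Statistical analysis) names three analysis sets. The full analysis set takes everyone with at least one RTOG assessment after randomisation. The per-protocol set is "the group of participants complying with the trial procedure, including the study drug use, at least 80" per cent. For the third, "Safety set is defined as the participants who use the study drug at least once".

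On the test, the same section says: "The adverse events will be tested with Chi-square or Fisher exact test". The next sentence gives within-group comparison of vital signs to the paired t test or the McNemar test.

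On who receives the drug, section 2.4 says that "JUG will be prescribed only to participants of the JUG treatment group", and section 2.2 says: "Both groups will be subjected to GSC, but only the JUG group will apply the adjuvant JUG ointment on the irradiated skin". There is no placebo. Section 2.3 uses the term study drug for the product to which a patient might be hypersensitive ("history of hypersensitivity reaction to the study drug"), and section 2.5 describes dispensing, diary and bottle return for JUG only.

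On the aim, the Introduction describes the trial as directed at "showing the effectiveness and safety of the adjuvant application of JUG for RD in breast cancer patients undergoing RT, as compared to GSC".

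**The concern.** A safety set defined by exposure to the study drug works when every arm receives a study drug or a placebo. Here the control arm receives neither, so the rule removes the whole control arm from the safety population.

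This matters more than usual in this trial. Section 2.11 expects local rash, redness and itching with the ointment. Section 2.8 grades radiation dermatitis by eruption, erythema and itching. The expected drug reactions and the effect of radiotherapy therefore look alike, and only patients irradiated without JUG can show how much of the local reaction would have occurred anyway. A safety analysis confined to JUG users cannot separate the two.

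The per-protocol definition shows a milder form of the same problem. One component of its 80% rule, use of the study drug, has no counterpart in the GSC arm.

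**Working it through.** **1. The plan's group sizes.** Section 2.13 gives event-free proportions of 53.3% (JUG) and 21.4% (GSC), two-sided alpha 0.05, power 80% and 10% drop-out.

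- Hazard ratio = ln(0.533) / ln(0.214) = 0.408.
- Freedman events = (1.960 + 0.842)² × ((1 + 0.408) / (1 − 0.408))² = 44.4, rounded up to 45.
- Mean event probability = 1 − (0.533 + 0.214) / 2 = 0.6265.
- Total = 45 / 0.6265 = 71.8, that is 36 per group.
- With drop-out, 36 / 0.9 = 40 per group, 80 in all.

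The stated 36 and 40 per group reproduce. Nothing in this point changes them.

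**2. Counting the safety set by arm.**

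| Definition | JUG | GSC |
|---|---|---|
| As written (used the study drug at least once) | up to 40 | 0 |
| All randomised who start radiotherapy, by treatment received | up to 40 | up to 40 |

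The second row assumes that everyone starts radiotherapy and that every JUG patient applies the ointment at least once. If 10% were lost from each arm, it would be about 36 and 36.

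**3. What the test does with an empty arm.** The article gives no adverse-event rates, so these counts are assumed for illustration.

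- 6 of 40 in JUG and 0 of 0 in GSC: the Chi-square test fails because expected counts are zero. Fisher's exact test returns an undefined odds ratio and p = 1, which says nothing about safety.
- 6 of 40 in JUG and 2 of 40 in GSC: Fisher's exact test gives p = 0.26, an ordinary usable result.

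**4. Is the adverse-event test meant to be between groups?** The sentence does not say so, but the context does. Chi-square and Fisher tests compare independent groups, and the trial has only two. The within-group tests are named separately, for vital signs. The Introduction makes safety against GSC an aim.

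**5. The per-protocol component.** The treatment period is 42 days, and 80% of 42 is 33.6 days. Suppose a JUG patient uses the ointment fully until stopping. Stopping after 33 days gives 33/42 = 78.6%, which fails the drug-use component; stopping after 35 days gives 35/42 = 83.3%, which passes. A JUG patient who stops early because of dermatitis could therefore be removed together with the event, whereas a GSC patient has no drug-use threshold to miss. The article gives no stopping rates, so the size of any effect cannot be derived from it.

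**The case against.** **The adverse-event sentence names no analysis set.** The test could be run in the full analysis set, and section 2.11 has adverse events recorded during the study without restriction to JUG users. This stands in part. A reader might infer that control-arm safety data are lost or that no comparison is possible at all; the article does not support that. The fault lies in the definition of a set. Still, a safety set exists for safety analysis, and as defined it cannot serve the comparison. The full analysis set is a poor substitute, because it drops anyone who leaves before a first RTOG assessment.

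**An article condenses the full protocol.** That would answer a missing detail. Here the definition is given, and it conflicts with the article's own test and aim.

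**The per-protocol rule covers more than drug use.** This stands. A reader might infer that the per-protocol set filters only the JUG arm and is biased in favour of JUG. The article supports neither. The 80% applies to the trial procedure as a whole. Section 2.6 gives skin-care instructions to both arms and bars other management of radiation dermatitis in both. A GSC patient who turned to something barred after developing dermatitis might also leave the set with the event, which could offset or reverse the bias. No passage says that patients stop JUG on reaching grade 2. What remains is that one component binds one arm only and could depend on the outcome.

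**Nothing primary is touched.** This also stands. The primary analysis uses the full analysis set, which treats both arms alike, and the per-protocol analysis is secondary.

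**Conclusion.** The safety set is wrong as written: up to 40 JUG patients, 0 GSC patients, and so no comparator for the planned adverse-event test in that set. The count rests on two readings, both well supported by the article: that the study drug means JUG, and that the adverse-event test is between groups and belongs in the safety set. The rule conflicts with the stated aim of assessing safety against GSC.

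The per-protocol point is minor. The filter is asymmetric in its drug-use component, with unknown direction and size, and no figure for bias or false-positive rate should be attached to it.

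The primary analysis, the sample size and, as far as the article shows, data collection are unaffected. The correction should be made, and preferably before adverse-event data are examined: the trial is open-label, so a later change of population would look post hoc.

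**What to change.** Replace the safety-set sentence with one that includes both arms: all randomised participants who start radiotherapy, analysed by treatment actually received (any JUG applied versus GSC only). Add that adverse events are compared between arms in this set with the Chi-square or Fisher test. If anyone applies JUG but never starts radiotherapy, list that person's adverse events separately so that they are not lost.

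For the per-protocol set, it is enough to state that its result is supportive only.

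The cost is one or two sentences, with no new data, no further patients and no change to the 36 per group or the total of 80.

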### Ethics and dissemination

2.15

The study protocol and the informed consent form have been reviewed and approved by the Institutional Review Board in Kyung Hee University Korean Medicine Hospital, Republic of Korea (KOMCIRB-2018-10-003) on 14 December 2018 (Protocol V1.3) and registered in Clinical Research Information Service (CRIS, https://cris.nih.go.kr/cris/en/, KCT0003506) on 14 February 2019. Any amendments of protocol and consent forms will be valid only after being reviewed and approved by the Institutional Review Board in Kyung Hee University Korean Medicine Hospital and be publicized via CRIS.

Medical doctors will give the full information to any potential participant and obtain the written consent. Any data of the enrolled participants will be collected only with screening/random codes and their initials. Any personal information including identification code and their names will not be recorded in the case report forms nor shared with others.

The datasets used and/or analyzed after completing the current study will be available from the corresponding author under reasonable requests. The investigators will disseminate the study results and implications via publication.

## Discussion

3

This is a prospective, open-label, parallel-group, randomized controlled trial to evaluate the effectiveness and safety of adjuvant application of JUG for RD in breast cancer patients undergoing RT, and compare with GSC. Eighty female patients with unilateral breast cancer after breast conserving surgery will be allocated to either JUG or GSC groups with an allocation ratio of 1:1. Both groups will undergo GSC, but only the JUG group will apply the adjuvant JUG ointment on the irradiated skin for 6 weeks, twice a day. Pharmacoeconomic evaluation of JUG will also be investigated.

JUG is a herbal ointment that has been authorized as a drug for xerosis cutis, frostbite, miliaria, anal fissure, and rhus dermatitis by the Ministry of Food and Drug Safety of the Republic of Korea.^[11]^ In clinical practice, many TKM doctors have used JUG for a variety of dermatopathy symptoms. With respect to the experimental evidences,^[12,13,15–17]^ we assumed that there could be a positive possibility to use JUG for RD. We have learned the effect size from the pilot study and expect significant results from this full-scale clinical trial.
